## Methods

### Study design

The FURTHER trial is a multicenter three-armed randomized controlled superiority trial, performed in six hospitals in four European countries, all of which are partners in the FURTHER consortium. The trial will be coordinated from the UMC Utrecht, with a steering group consisting of representatives of all institutions and an external advisory board. The design and report of this protocol follow the Standard Protocol Items: Recommendations for Interventional Trials statement. [26]

After inclusion, patients are randomized in a 1:1:1 ratio to one of the three intervention arms and will receive either standard EBRT, MR-HIFU only, or combined EBRT and MR-HIFU (Fig. 1). Treatment will be delivered as soon as possible. A total of 216 patients will be randomized, 72 patients into each arm of the trial.

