**Secondary outcomes**	
2.1. Patient-reported pain scores	Assessed using the BPI and patient pain diary during the first 21 days, at 4 and 6 weeks and 3 and 6 months following treatment
2.2. Physician reported toxicity	Assessed by telephone call at 3 days; 1, 4, and 6 weeks; and 3 and 6 months following completion of treatment according to the Common Terminology Criteria for Adverse Events (CTCAE) version 5.0
2.3. Patient-reported quality of life	Assessed using the EORTC QLQ BM22, C15-PAL, EQ-5D-5L, and PGIC at baseline; 1, 2, and 4 weeks; and 3 and 6 months following completion of treatment
2.4. Local tumor control	Assessed using CT and/or MRI imaging at patient discretion at 3 and/or 6 months after completion of treatment
2.5. Levels of anxiety and depression	Assessed among patients, patients’ partners, and caregivers by the Hospital Anxiety and Depression Scale (HADS) and EDIZ-list at baseline; 1, 2, 4, and 6 weeks; and 3 and 6 months following completion of treatment
2.6. Cost-effectiveness of the treatment	Assessed as cost per responder and cost per quality-adjusted life years (QALY), from a payer perspective, at 6 months of follow-up

Pain response will be based on the numeric rating scale (NRS) and the pain severity index calculated from the Brief Pain Inventory (BPI) questionnaire [28, 29]. In addition, analgesic and anti-neuropathic drug use is recorded, and all opioid analgesics are expressed as the oral morphine equivalence dose (OMED). The primary endpoint of the trial will follow the International Consensus on Palliative Radiotherapy Endpoints for Future Clinical Trials in Bone metastases [30]. In accordance with the consensus, pain will be assessed by the worst pain score over the previous 3 days. Patients will be categorized as responders when either a reduction of pain score of at least 2 points without increase of analgesic intake is achieved, or a reduction of analgesic intake of at least 25% is accomplished without an increase of pain score at the treated site. All other patients will be categorized as non-responders.

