**Fig. 2 Fig2:**
[figure not shown]
Schematic overview of the follow-up timelines for the FURTHER trial illustrating the start and end of follow-up. In addition, the primary endpoint and secondary endpoint 14 days after inclusion are visualized. For all three arms, i.e., external beam radiotherapy (EBRT), magnetic resonance-guided high-intensity focused ultrasound (MR-HIFU), and EBRT + MR-HIFU, the follow-up is started after the first treatment session

Patients are free to leave the study at any time. Patients will be followed until death or end of study (6 months). To reduce the impact of patient death on loss to follow-up, the inclusion criteria “life expectancy > 3 m” was added. To further minimize missing data, patients will be actively contacted by phone on scheduled times to remind them of filling in the questionnaires. No specific dropout criteria are defined. The investigator can decide to withdraw a patient from the study for urgent medical reasons. Patients will be considered non-responders when they will be referred to alternative palliative treatments of the treated metastasis (such as (re)irradiation, radiopharmaceuticals, surgery, cryotherapy, radio-frequency ablation or nerve blocks, or MR-HIFU in the EBRT arm).

Since this study concerns a one-off treatment, patients will return to their general practitioner or referring oncologist. All participating centers have insurance that covers damage to research subjects through injury or death caused by the study. The insurance applies to damage that becomes apparent during the study or within 4 years after the end of the study.

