During treatment preparation, the skin overlying the site of interest will be shaved and premedication (consisting of analgesics) will be administered. The procedure will be done using either procedural sedation and analgesia or general anesthesia. Patients will be positioned to obtain an HIFU beam path as perpendicular to the cortical bone surface as possible. After treatment planning and patient positioning, a low-energy sonication test will be performed to confirm reachability and correct for potential HIFU beam path distortion. Maintaining a temperature of at least 55 °C for 1 s as measured by MR thermometry in front of the cortical bone is considered to deliver a thermal dose high enough to achieve adequate ablation of the periosteum [36, 37]. During treatment, real-time temperature mapping will be used to monitor whether this goal was achieved and to determine the completion of treatment. Preferably full lesion surface coverage will be achieved by systematically sonicating treatment cells in a contiguous way, respecting system-recommended cooling times between sonications. After the HIFU procedure, a contrast-enhanced T1w-scan using a gadolinium-based standard MR contrast agent will be acquired to evaluate the treatment effect. The patients are then transferred to the recovery room or patient ward for medical supervision. When the patient has recovered from procedural sedation and no complications have occurred, the patient can be discharged on the same day. Alternatively, patients may, at the discretion of the treating physician, stay overnight at the hospital. The MR-HIFU treatment exists in one session, and the treatment duration is several hours, depending on lesion size and location. The MR-HIFU procedure has a good safety profile: there is a small risk of minor treatment-related side effects including pain in the treated area, first-/second-degree skin burns, and bruising. Severe side effects are extremely rare and include necrosis of nontarget tissue, ulcerating skin burns, and anesthetics-related complications [13]. These side effects will be monitored during hospitalization and follow-up phone calls. If MR-HIFU treatment does not alleviate pain within 4 weeks after treatment, patients will be offered standard care (EBRT).

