### Statistical analysis

All statistical analyses will be performed using IBM SPSS statistics, version 24 (IBM Corp. Armonk, NY, USA) and R version 4.0.4 (R foundation for statistical computing; https://R-project.org/). Data characterized by normal distribution will be expressed as means with standard deviations. Parameters not normally distributed will be expressed as medians with the interquartile ranges. Data will be analyzed according to the intention to treat and per-protocol principle. In case of post-treatment dropout (i.e., patients not surviving longer than a week, or patients unable to provide pain scores and analgesic use), a worst-case analysis will be performed, where dropped-out patients will be classified as non-responders.

The domain of the primary outcome is pain response measured by the Brief Pain Inventory (BPI [28, 29]) at baseline and 14 days following the start of treatment. Pain response is defined as a reduction of pain score ≥ 2 points without an increase of analgesic intake, or a reduction of analgesic intake of ≥ 25% without an increase of pain score at the treated site. The method of aggregation is the proportion of patients with a complete or partial pain response between baseline and 14 days following the start of treatment. Differences in pain response between arms will be compared by *χ*^2^-test. We will also conduct a time-to-event analysis for pain response. Here, the method of aggregation is the median time to pain response. Survival analysis will be performed by the Kaplan–Meier estimate and is calculated as the number of subjects surviving divided by the number of patients at risk (proportion). Survival proportions will be compared at 6 months. Toxicity will be presented as the proportion of CTCAE grade 3–4 toxicity in the 6 months following the start of treatment and differences will be tested with the *χ*^2^-test. QoL will be expressed as the mean (or median) score on a scale of 0–100 (EORTC [31–35]) and compared between the three groups at 3 and 6 months after treatment starts. A mean change of 10% of the scale breadth from the baseline will be considered a clinically relevant change in QoL. We will evaluate the pattern of QoL as a continuous outcome over time using mixed models. Differences with a *P*-value of < 0.05 will be considered statistically significant. No additional subgroup analyses are planned.

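### The toxicity comparison stops at CTCAE grade 4, so a patient whose only severe treatment-related event is fatal is not counted in it

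*Protocol article*

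**What the plan says.** Four places in the protocol article bear on this.

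- **Statistical analysis, toxicity.** The outcome and its test are set in one sentence: "Toxicity will be presented as the proportion of CTCAE grade 3–4 toxicity in the 6 months following the start of treatment", with arms compared by a chi-square test. The range has an upper end, grade 4.
- **Table 1, outcome 2.2.** Physician-reported toxicity is collected by telephone under the "Common Terminology Criteria for Adverse Events (CTCAE) version 5.0". No grade is excluded at collection.
- **Statistical analysis, survival.** Deaths are handled by Kaplan–Meier estimation: "Survival proportions will be compared at 6 months". Nothing is said about cause of death or relation to treatment.
- **MR-HIFU treatment.** On the harms of the procedure: "Severe side effects are extremely rare and include necrosis of nontarget tissue, ulcerating skin burns, and anesthetics-related complications". No rate is given, and the sentence concerns MR-HIFU only.

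No sentence adds grade 5 events to the toxicity proportion or says that they will be tabulated by arm.

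**The concern.** A severe-toxicity outcome should not improve when a harm gets worse. With an upper limit at grade 4, it can: a complication survived at grade 4 counts against the arm, and the same complication ending in death does not.

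This matters more here than in a trial whose arms carry similar procedural risk. Two of the three arms receive an ablative procedure under procedural sedation or general anaesthesia, and the control arm does not. The protocol itself lists anaesthetic complications among the severe effects. The trial is meant to show whether MR-HIFU can replace or supplement radiotherapy, so the severe-toxicity comparison will be read as a main part of its safety evidence.

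**Working it through.** The plan states no expected toxicity rate, so there is no figure to reproduce. The check has two parts.

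**1. Where a fatal treatment-related event goes.** Three patients, each with one severe treatment-related event, are followed through the stated outcomes:

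| Worst event | Collected (Table 1, 2.2) | Toxicity proportion | Survival at 6 months |
|---|---|---|---|
| Grade 3 | yes | counted | alive, unless death from another cause |
| Grade 4 | yes | counted | alive, unless death from another cause |
| Grade 5 only | yes | not counted | counted as a death, cause not stated |

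The gap arises only in the analysis sentence. A patient who had a separate grade 3 or 4 event before a fatal one is still counted, so the gap is confined to patients whose only severe event is grade 5.

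**2. How much one event weighs.** The input from the Study design section is 72 patients per arm. The severe-event rate p is an assumption, because the article gives none; the range used is 1% to 10%.

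Expected events per arm = 72 × p:

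| p | 1% | 2% | 3% | 5% | 7% | 10% |
|---|---|---|---|---|---|---|
| Events | 0.7 | 1.4 | 2.2 | 3.6 | 5.0 | 7.2 |

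If an arm has k patients with grade 3–4 events and one more patient whose only severe event is grade 5, the plan reports k/72 where (k + 1)/72 had severe toxicity. The shortfall is always 1/72 = 1.4 percentage points:

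- k = 0: 0% reported, 1.4% actual
- k = 1: 1.4% reported, 2.8% actual
- k = 3: 4.2% reported, 5.6% actual
- k = 6: 8.3% reported, 9.7% actual

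One event can also move the test result. Take assumed counts for two arms of 72, with the uncorrected chi-square test. Suppose one arm has 1 grade 3–4 event, and the other has 6 grade 3–4 events and 1 fatal event.

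- Fatal event left out, 1 v 6: pooled proportion 7/144 = 0.0486; χ² = (5/72)² / [0.0486 × 0.9514 × (2/72)] = 3.75; P = 0.053.
- Fatal event included, 1 v 7: pooled proportion 8/144 = 0.0556; χ² = (6/72)² / [0.0556 × 0.9444 × (2/72)] = 4.76; P = 0.029.

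Fisher's exact test gives 0.116 and 0.063 for the same tables, so the crossing of 0.05 belongs to this example under the planned test and is not general. What holds generally is the direction: leaving out a fatal event always favours the arm in which it occurred.

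**The case against.** The strongest reply is that the death is not lost. The abstract lists adverse events and survival as secondary outcomes separate from toxicity. Serious adverse events are collected throughout, and survival is compared at 6 months. All-cause mortality by randomised arm is a valid comparison that needs no judgement of cause. In addition, the worst-case rule classes patients who do not survive longer than a week as non-responders, so an early peri-procedural death counts against its arm on pain response.

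All of that stands, and it limits the point. A reader might infer that a fatal complication vanishes from every comparison between arms. The documents do not support that; it is missing from the toxicity proportion only. The other routes still do not close the gap. Survival mixes toxic deaths with cancer deaths in an advanced-cancer population, where one treatment-related death would be hard to see. The worst-case rule records a failed pain response, not a harm.

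A reader might also infer that the chi-square test is wrong because events will be too few. That is not supported either.

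- Sparseness is an assumption. The remark on rarity covers MR-HIFU alone, while the outcome counts grade 3–4 toxicity in all arms over 6 months. Expected counts fall below 5 per arm only if the rate is under 5/72 = 6.9%.
- By exact enumeration over 1–10%, the three-arm chi-square test at nominal 0.05 has a true size of 0.026 to 0.049, so it holds its level.
- Single tables can disagree: for 3, 0 and 0 events, chi-square gives P = 0.048 and the exact test 0.108. But Fisher's test for 72 v 72 has a size of only 0.0001 to 0.026 over the same range, so it would make a harm harder to flag.
- A fallback test for small counts is commonly left to the statistical analysis plan, which is not shown.

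That last argument does not rescue the grade limit. The article does not leave the grade range open; it states one that ends at grade 4.

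**Conclusion.** The point holds for the definition of the outcome. As written, the toxicity proportion excludes a patient whose only severe treatment-related event is grade 5, and no other stated comparison attributes that death to treatment. The size is 1.4 percentage points per uncounted event in an arm of 72. That is small in absolute terms but can be a large share of an arm's total if severe toxicity is as uncommon as the assumed 1–5%. If no such death occurs, nothing changes.

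The conclusion rests on the standard CTCAE meaning of grade 5, which the article adopts by naming the scale but does not spell out, and on reading the stated grade range literally. It concerns a secondary outcome and leaves the primary analysis untouched. The choice of the chi-square test is not an error.

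**What to change.** In the Statistical analysis section, define the toxicity outcome as the proportion of patients with at least one CTCAE grade 3 or higher event (grades 3–5) in the 6 months from start of treatment. Add that grade 5 events will be shown separately by arm.

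The cost is one or two lines of wording. Collection already covers all grades and patients are followed until death, so no new data are needed, and the sample size and primary analysis stay as they are. The change is best made before outcome data are examined by arm, since widening the definition after a death is known would be open to challenge. Naming an exact test for sparse counts is optional and not part of this correction.

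### The only stated toxicity comparison starts at CTCAE grade 3, so the minor MR-HIFU skin effects that the protocol expects probably enter no stated comparison between arms

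*Protocol article*

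**What the plan says.** The protocol article deals with toxicity in three places.

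- **Collection.** Table 1, outcome 2.2, has physicians report toxicity from phone contacts at six time points, the first on day 3 and the last at 6 months, graded "according to the Common Terminology Criteria for Adverse Events (CTCAE) version 5.0". No grade limit is set. The follow-up table (Table 3) also has an adverse-event row at every contact from day 3 to 6 months.
- **Expected harms.** The MR-HIFU treatment section says that "there is a small risk of minor treatment-related side effects including pain in the treated area, first-/second-degree skin burns, and bruising". It then says: "Severe side effects are extremely rare and include necrosis of nontarget tissue, ulcerating skin burns, and anesthetics-related complications". Both kinds are followed: "These side effects will be monitored during hospitalization and follow-up phone calls".
- **Analysis.** The Statistical analysis section states a single toxicity measure: "Toxicity will be presented as the proportion of CTCAE grade 3–4 toxicity in the 6 months following the start of treatment". Differences between arms are tested with a chi-square test.

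The article states no summary or comparison of toxicity below grade 3. The Abstract lists adverse events beside toxicity as a secondary outcome, but the article states no analysis of adverse events.

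**The concern.** The lower cut-off of the stated analysis does not fit the protocol's own description of risk. The harms expected from MR-HIFU fall in the class called minor, while the analysis keeps a range that, for MR-HIFU side effects, is expected to be nearly empty.

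The Objectives section asks whether MR-HIFU has a place as a substitute for EBRT or as an addition to it. The Discussion says that effectiveness and safety have not been compared in a randomised trial in the first-line setting. Burns and bruising are part of the cost that a patient would set against faster pain relief. If the only toxicity contrast is at grade 3–4, a non-significant result may be reported as no difference in toxicity while a real excess of lower-grade skin effects goes uncompared.

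**Working it through.** **Step 1: which harms reach which comparison.** The protocol assigns no CTCAE grades, so reading minor as mostly below grade 3 is an inference from its split between minor and severe.

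| Harm named in the MR-HIFU treatment section | Protocol's class | In the grade 3–4 comparison? | In another stated comparison? |
|---|---|---|---|
| First- or second-degree skin burns | minor | only if graded 3 or 4 | none as a harm |
| Bruising | minor | only if graded 3 or 4 | none as a harm |
| Treated-area pain | minor | only if graded 3 or 4 | pain scores and pain response, not as a harm |
| Nontarget necrosis, ulcerating burns, anaesthetic complications | severe, extremely rare | yes, if graded 3 or 4 | not needed |

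The gap is therefore mainly burns and bruising.

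**Step 2: numbers of patients.** From Study design: "A total of 216 patients will be randomized, 72 patients into each arm of the trial". The two MR-HIFU arms together have 2 × 72 = 144 patients, against 72 on EBRT. The Sample size calculation section pools these two arms for the primary endpoint. Pooling them for toxicity is my assumption.

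**Step 3: illustration of size.** The protocol states no toxicity rate, so there is no figure to reproduce, and every rate below is an assumption. The test statistic is

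z = (a/144 − b/72) / √[p(1 − p)(1/144 + 1/72)], with p = (a + b)/216,

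where a and b are the numbers of patients affected. A difference is declared when |z| > 1.96. Power is the sum of the binomial probabilities of all pairs (a, b) that meet this rule.

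| Measure | Assumed MR-HIFU v EBRT | Expected patients | Power |
|---|---|---|---|
| Grade 3–4 | 2% v 1% | 2.9 v 0.7 | 0.014 |
| Grade 3–4 | 5% v 2% | 7.2 v 1.4 | 0.12 |
| Any grade | 5% v 1% | 7.2 v 0.7 | 0.23 |
| Any grade | 10% v 5% | 14.4 v 3.6 | 0.22 |
| Any grade | 15% v 5% | 21.6 v 3.6 | 0.61 |
| Any grade | 20% v 10% | 28.8 v 7.2 | 0.47 |
| Any grade | 20% v 5% | 28.8 v 3.6 | 0.90 |

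If the true grade 3–4 rate were 1%, the chance of seeing no such patient would be 0.99^72 = 0.485 in one arm and 0.99^144 = 0.235 in both MR-HIFU arms together.

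**Step 4: background events.** The stated measure is not limited to treatment-related events, so disease-related grade 3–4 events may raise the proportion in every arm. At an assumed background of 20%, a 2-point excess (22% v 20%) has power of about 0.06. A higher background does not make the grade 3–4 comparison more informative about MR-HIFU harms.

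**Step 5: what an interval would show.** For an assumed 15% v 5%, the standard error is √(0.15 × 0.85/144 + 0.05 × 0.95/72) = 0.039. The 95% interval for the 10-point difference is about 10 ± 7.7, or 2 to 18 points. For 10% v 5% it is 5 ± 7.0, or −2 to 12 points. Even the weaker case tells a reader something that a grade 3–4 row cannot.

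**The case against.** **Full reporting may be specified elsewhere.** The Abstract separates adverse events from toxicity, Table 3 collects adverse events at each contact, and an article commonly leaves tabulation to the full protocol or SAP. This stands in part: nothing says that lower-grade events will go unreported, and all-grade tables may be planned. But the article is not silent on the toxicity analysis. It states the measure and the test, and that stated cut-off is the point here.

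**A reader might infer that the known harms never reach any comparison.** The text does not support this. Treated-area pain is measured daily for 21 days and then at the later visits, and it feeds pain response and pain scores, so a procedure-related rise would count against MR-HIFU there. The severe harms enter if they are graded 3 or 4. Quality of life is compared across arms and could reflect harms indirectly.

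**A reader might infer that the toxicity result will be near 0% in every arm.** This is also unsupported. Extremely rare describes severe side effects of MR-HIFU only. No rate is given for EBRT or for combined treatment, and in patients with metastatic cancer followed for 6 months grade 3–4 events from other causes may be common.

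**The power figures prove little.** The protocol speaks of a small risk of minor effects. Under low rates that fit this wording, an any-grade test has only about 22–23% power. That is right: the figures illustrate and carry no conclusion. The proposed table is descriptive and does not depend on power.

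**A grade 3–4 summary is a defensible prespecified measure.** It is, and it should stay. The weakness is that it stands alone.

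**Conclusion.** The concern holds in a limited form. The one stated toxicity comparison is at grade 3–4, although toxicity is collected at all grades and the expected MR-HIFU effects are described as minor. On the inference that minor mostly means below grade 3, expected burns and bruising have no stated arm comparison, and treated-area pain is compared only as an efficacy outcome. The risk lies in interpretation: a non-significant grade 3–4 result could be taken as no difference in toxicity. Its size cannot be derived from the document, which gives no toxicity rates; the assumed-rate powers show only that the two measures can carry very different information.

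No stated analysis becomes invalid and the primary endpoint is unaffected. This is a cheap improvement.

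**What to change.** Keep the grade 3–4 proportion and its test. Add to the Statistical analysis section, or confirm in the SAP, wording such as:

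*Toxicity will also be tabulated by arm as the number and proportion of patients by worst CTCAE grade and with toxicity of any grade. Each MR-HIFU risk named in this protocol (treated-area pain, skin burn, bruising, nontarget tissue necrosis, anaesthetic complications) will be shown at any grade, with the difference from EBRT and its 95% confidence interval. These comparisons are descriptive.*

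No significance claims should be added. Fixing the list before the data are analysed avoids a later choice of which harms to show.

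The cost is two or three sentences and one table from data already planned for collection, with no change to treatment, visits or sample size. The downside is a longer report and a possibly less favourable MR-HIFU safety profile.
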